# Effectiveness of adjuvant radiotherapy in patients with oropharyngeal and floor of mouth squamous cell carcinoma and concomitant histological verification of singular ipsilateral cervical lymph node metastasis (pN1-state) - A prospective multicenter randomized controlled clinical trial using a comprehensive cohort design

**DOI:** 10.1186/1745-6215-10-118

**Published:** 2009-12-23

## Abstract

**Background:**

Modern radiotherapy plays an important role in therapy of advanced head and neck carcinomas. However, no clinical studies have been published addressing the effectiveness of postoperative radiotherapy in patients with small tumor (pT1, pT2) and concomitant ipsilateral metastasis of a single lymph node (pN1), which would provide a basis for a general treatment recommendation.

**Methods/Design:**

The present study is a non-blinded, prospective, multi-center randomized controlled trial (RCT). As the primary clinical endpoint, overall-survival in patients receiving postoperative radiation therapy vs. patients without adjuvant therapy following curative intended surgery is compared. The aim of the study is to enroll 560 adult males and females for 1:1 randomization to one of the two treatment arms (irradiation/no irradiation). Since patients with small tumor (T1/T2) but singular lymph node metastasis are rare and the amount of patients consenting to randomization is not predictable in advance, all patients rejecting randomization will be treated as preferred and enrolled in a prospective observational study (comprehensive cohort design) after giving informed consent. This observational part of the trial will be performed with maximum consistency to the treatment and observation protocol of the RCT. Because the impact of patient preference for a certain treatment option is not calculable, parallel design of RCT and observational study may provide a maximum of evidence and efficacy for evaluation of treatment outcome. Secondary clinical endpoints are as follows: incidence and time to tumor relapse (locoregional relapse, lymph node involvement and distant metastatic spread), Quality of life as reported by EORTC (QLQ-C30 with H&N 35 module), and time from operation to orofacial rehabilitation. All tumors represent a homogeneous clinical state and therefore additional investigation of protein expression levels within resection specimen may serve for establishment of surrogate parameters of patient outcome.

**Conclusion:**

The inherent challenges of a rare clinical condition (pN1) and two substantially different therapy arms would limit the practicality of a classical randomized study. The concept of a Comprehensive Cohort Design combines the preference of a randomized study, with the option of careful data interpretation within an observational study.

**Trial registration:**

ClinicalTrials.gov: NCT00964977

## Background

Ninety percent of all tumors in the head and neck region are of squamous cell origin and world wide annual incidence is estimated at 363.000 with a mortality of 200.000 [1,2]. Oropharyngeal squamous cell carcinoma (OSCC) is the predominant malignancy in the head and neck region, and is the seventh most frequently occurring tumor world-wide. In the Federal Republic of Germany, up to 3-5% of all malignant tumors are found within the oral cavity and the oropharynx, with 7.500 new cases annually. 2.2% cases of death occur as a consequence of oropharyngeal malignancy [3]. Thus, treatment of patients with OSCC is of great medical and economic importance. Prevailing curative therapeutic strategies combine radical resection of the tumor with a safety margin, followed by radiation of the original tumor site and adjacent locoregional lymphatic drainage areas [4-6]. To date, selection of the individual therapeutic pattern is essentially guided by pre- and post-therapeutic TNM staging parameters. Particularly for advanced tumors, postoperative radiotherapy, possibly combined with chemotherapeutic agents, is favorable and recommended [7-9]. Interdisciplinary guidelines state the following detailed recommendations for application of adjuvant radiation therapy:

- non in sano resection if reoperation is impossible (R1-, R2-status)

- primary tumor status > pT2 and pN2, pN3

- extranodular spread of the disease

- lymphangiosis carcinomatosa

- facultative: pN1

According to these recommendations, postoperative radiotherapy of advanced tumors is advised, while for small tumors the indication depends on further parameters such as the pN- state. In these cases, verification of metastasis in more than a single lymph node (pN2) leads to additional radiotherapy. In tumors with a diameter of less than 4 cm (T1, T2) and concomitant verification of a single lymph node metastasis, no explicit therapeutic recommendation is presently offered, leaving radiation as an optional complement for these cases. Meta-Analysis revealed only a few studies taking this special group of patients into account, the results of which suggest that adjuvant radiotherapy is an additional risk factor for overall survival. However, the small patient count, inhomogeneous group distribution and ambiguous risk factors in these studies contribute to a substantial bias. Due to the emerging importance of quality of life information, the overall survival rate is not the only parameter of interest when reviewing the effectiveness of modern tumor therapy. Therefore, there is urgent need for controlled studies verifying the effect of postoperative radiotherapy. The aim of the present study is to investigate the clinical outcome in patients with or without postoperative radiotherapy after curative intended radical surgery, because meta-analysis of present retrospective clinical data failed to support a safe and justifiable treatment regime in patients with small tumor (T1, T2) and a single ipsilateral lymph node metastasis.

The following key methodological problems have to be addressed in the protocol:

• extremely different treatment arms with strong preferences for one or the other therapy arm

• low number of eligible patients per center

• Inclusion criterion (pN1), including a pathological diagnosis and surgical treatment with possible differences

• Radiation treatment as one arm with special quality control needs

The purpose of presenting this paper is to discuss how these specific issues were addressed.

## Methods/Design

### Study Design

The study is designed as a non-blinded, prospective, randomized controlled clinical trial. Study approval was given by the Ethics Committee of the State Medical Council of Rhineland-Palatinate, Germany [Ref. No: 837.148.03 (3810)]. As part of the Johannes Gutenberg-University, the Coordination Center for Clinical Trials (KKS Mainz, Germany), will monitor the study progress and assure data accuracy. Obvious side effects of radiation therapy render blinding of patients and examiner impossible.

### Study objectives

The objective of the clinical study will be to investigate two different patient groups (irradiated/unirradiated) with pT1/2 primary and verification of a singular ipsilateral lymph node metastasis in parallel design in order to evaluate the possible benefit of radiation therapy. Subsequent investigation of biological parameters will be performed to assess the capacity to predict tumor progression and to evaluate surrogate markers of radioresistance. The following null hypothesis forms the basis of the present study: Radiation therapy will have no influence on the overall survival in patients with pT1/2, pN1 primary tumor. Secondary outcome variables include incidence and time to tumor relapse (locoregional relapse, lymph node involvement and metastatic spread), Quality of life as reported by EORTC (QLQ-C30 with H&N 35 module) and time from operation to orofacial rehabilitation.

### Patients

Males and females with a histologically verified diagnosis of a primary squamous cell carcinoma of the oral cavity or the oropharynx are eligible. Inclusion criteria are as follows:

- maximum tumor diameter less than 4 cm in the pathohistological specimen irrespective of histological grading (pT1 or pT2)

- concomitant histological verification of a singular ipsilateral lymph node metastasis less than 3 cm in diameter (pN1) without penetration of the lymph node's capsule and without presence of lymphangiosis carcinomatosa

- radical resection of the tumor within adequate resection margins (R0)

- written informed consent from the patient

- adequate performance status ECOG Index ≤ 2

Patients younger than 18 and pregnant women are to be excluded. Further criteria of exclusion are reported drug addiction or intake of remedies with a potential influence on compliance or impaired judgment. In addition, patients with familial or job related responsibilities which may preclude the patient from maintaining the study schedule, as well as patients with inadequately treated diseases, such as untreated diabetes mellitus or acute heart insufficiency (ECOG-Index>2), will also be excluded.

### Study interventions

Radiotherapy should begin within 6 weeks after the last surgical intervention while respecting a minimal postoperative healing period of at least 8 days. Causes for delay of intervention are to be documented. In both the RCT and observational study, patients of group 1 will be treated by irradiation and patients of group 2 will not receive radiotherapy.

### Surgical treatment

The primary tumor is considered radically resected if macroscopic and histologic evaluation shows resection margins without tumor residuals (R0 status). For surgical proceeding, a safety margin of at least 0.5 cm is established. Lymph node resection will be oriented in relation to the tumor center, which can be localized in level I (below occlusional plane) or level II (above occlusional plane), in addition to being precanine, postcanine or retromolar (Figure 1). Infiltration of the periosteum and midline crossing is also characterized. Classification of cervical regions follows the recommendations of Robbins from 2002 [10]. Hence, the neck is divided into 6 different sections (Figure 2).

**Figure 1 F1:**
[figure not shown]
**According to Bier (1982) description of tumor position follows its relation to the occlusal plane, canine and the last molar in transversal, saggital and axial projection**.

**Figure 2 F2:**
[figure not shown]
**Definition of the cervival levels as defined by Robbins 1991**.

#### Ipsilateral N0 state of cervical lymph nodes

Pre- and post-canine localized tumors of level I require selective neck dissection of the cervical level 1-3. For Level I tumors of the retromolar triangle selective neck dissection of ipsilateral level 1-5 is proceeded. For level II tumors no selective neck dissection is considered.

#### Contralateral N0 state

No neck dissection is performed

#### Ipsilateral N1-N2 state

For retromolar localized level I tumors, a modified radical neck dissection is performed. If the tumor is localized, pre- or post-canine, intraoperative frozen sections of level 1 lymph nodes are evaluated. Positive intraoperative results lead to modified radical resection of level 1-5 lymph nodes, while negative results only require resection of the lymph nodes within level 1-3. Negative intraoperative frozen sections in level II tumors require no lymph node dissection, but all metastatic affection of level II-III lymph nodes lead to modified radical neck dissection.

#### Contralateral N1-N2 state

Frozen sections will be performed for level 1 lymph nodes. Modified radical neck dissection is performed in positive results, resection of level 1-3 lymph nodes is conducted in case of negative results. Incidence of metastasis in level 2-3 lymph nodes acquire modified radical neck dissection.

#### Lymph node therapy of midline tumors

Midline tumors require bilateral resection of lymph node echelons at risk. Bilateral modified neck dissection is performed for staging purposes if indicated. Contralateral lymph node dissection of the level 1-3 in precanine localized tumors is mandatory.

### Technical conditions and practical execution of radiation therapy

Radiotherapy is performed using photons of 4 to10 MeV or/and electrons of 6 to 15 MeV maximum energy. Individual 3-dimensional dose distribution calculations are mandatory and have to be made on the basis of a postoperative native computer tomography. All patients are to be treated while immobilized by a custom made face mask made of thermoplast or equivalent. Clinical target volume definition encompasses the original tumor site with a safety margin of 2 cm in each direction.

### Floor of mouth, anterior tongue

Irradiation of the anterior two third of the tongue as well as the anterior floor of mouth is irradiated by laterally opposing beams, while the maxilla is separated by insertion of a bite block.

### Oropharynx, buccal plane, soft palate confined to one side

For tumors of the buccal plane, the tonsilla, the soft palate and the retromolar triangle, two types of target volume planning may be applied.

An ipsilateral target volume for the primary is defined, including the lymph nodes of group IB, IIA and IIB. The irradiation technique recommended uses two wedge fields, typically angulated by 90 to 120 degrees. The ipsilateral node levels III-V are treated by an anterior portal down to the clavicle, while the contralateral neck is spared.

Tumors of the lateral and dorsal pharyngeal wall and their lymphatic drainage (levels II, III, IV and V) are irradiated bilaterally with opposing beams. Irrespective of technique used, 3-D conformal dose shaping is highly recommended.

### Dosage and fractionation

Target volume definition and dosage must be performed according to the rules of ICRU report 50. At the primary tumor site and at involved lymph node levels, a total dose of 59.4 Gy in 33 fractions within 45 days is scheduled, and for electively irradiated volumes, a total dose of 50.4 Gy in 28 fractions is scheduled. All fractions of 1.8 Gy are given five times per week. In case of machine break down, an additional fraction per week is recommended with a minimum 6 h interval between two fractions on the same day or on Saturday. Total treatment duration (including planned/unplanned interruptions) is to be documented in days. All patients must be available for intent to treat analysis.

Instead of the classical portal arrangements and dose distributions, intensity modulated radiotherapy using an inverse calculation algorithm may be used in experienced centers. Dose constraints for normal tissues are left to the discretion of the participating centers, but dose specification according to the RTOG protocol H 0022 is recommended [11]. These details will be given in a standard operation procedure.

### Follow-Up

The recruitment phase will last 4 years. The follow up will include physical examinations, ECOG index, and quality of life questionnaires collected at 3, 6 and 12 months post operative. Further follow up will be performed annually until the study end. This means that patients will be followed up for a minimum of 5 years and a maximum of 9 years.

### Randomization and Sample Size

The present study design consists of a two-armed, randomized controlled trial (RCT), but patients who refuse to participate in a randomized approach and who express a radiation preference will be included in a prospective observational study after giving informed consent. This parallel observational trial will follow the same treatment and observation protocol as the RCT. Patients who agree to the randomized trial will be randomized and stratified according to lymph node therapy (yes/no) as formulated by the DOESAK [12]. Randomization to the radiation group and control group will be done 1 to 1, with recruitment extending over a period of 4 years and ongoing, annual follow-up continuing until the trial ends, i.e. for at least 5 years for each patient. Sample size calculation will be performed for the two-sided log rank test at a significance level of 5%. Assuming exponential distributed survival with 45% survival within the control group and 55% within the radiation group after 5 years (as per results observed in the DOESAK collective), and a drop-out rate of 5% per year, 280 patients per group are required to detect a difference of 5% in overall survival with a power of 70%. To ensure proper power adjustment, an intermediate analysis of the true drop out rate will be conducted. Recruitment of at least 280 patients per group in the observational study will be pursued only in the unfortunate event that patient recruitment within the randomized trial fails.

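### The sample-size sentence names a 5% detectable survival difference, but its own inputs are 10 points apart; power for 5 points is about 24%, not 70%

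*Protocol article*

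**What the plan says.** The sample-size paragraph in the protocol article (Methods/Design, Randomization and Sample Size) fixes the following:

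- Test: "Sample size calculation will be performed for the two-sided log rank test at a significance level of 5" per cent.
- Survival: "Assuming exponential distributed survival with 45% survival within the control group and 55% within the radiation group after 5 years". These rates are attributed to results in the DOESAK collective.
- Drop-out: 5% per year. Allocation: 1:1.
- Conclusion: "280 patients per group are required to detect a difference of 5% in overall survival with a power of 70" per cent.

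The survival rates and the conclusion stand in one sentence. The Follow-Up section adds 4 years of recruitment and 5 to 9 years of follow-up per patient. The Abstract gives the matching total of 560 patients. The same 280 per group is also the target for the observational study if randomization fails. No section gives another derivation of the 5% or says what it refers to.

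**The concern.** 55 minus 45 is 10 percentage points, not 5, so the sentence contradicts itself on the effect the trial is sized for. Either the number of patients was computed for 10 points and the stated difference is wrong, or 5 points was the target and the trial is far too small. Only recalculation can separate the two.

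The detectable difference tells a reader what a non-significant result would mean. The trial addresses a situation in which, according to the Background, no explicit treatment recommendation exists. Taken at face value, the sentence offers 70% power for a 5-point survival benefit. If the real figure is near 24%, the trial would miss such a benefit about three times in four, and a null result could be read as evidence against a benefit that the trial was never able to detect.

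**Working it through.** **Inputs from the article.** Two-sided α = 0.05, log-rank test, 1:1 allocation, 280 per group, exponential survival, 5-year survival of 45% and 55%, drop-out 5% per year, recruitment 4 years, follow-up 5 to 9 years.

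**Assumptions not in the article.** Uniform accrual, and drop-out as exponential censoring.

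**Formulas**

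- Hazard: λ = −ln(S₅)/5. Drop-out rate: η = −ln(0.95) = 0.0513 per year. Let r = λ + η.
- Probability of an observed death: P = (λ/r) × (1 − m), where m = (e^(−5r) − e^(−9r))/(4r) is the mean of e^(−rt) over follow-up times of 5 to 9 years.
- Deaths: d = 280 × (P_control + P_radiation).
- Power (Schoenfeld): Φ(|ln HR| × √(d/4) − 1.96).
- Deaths for 70% power: 4 × (1.96 + 0.524)² / (ln HR)².

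**Step 1. Reproduce the article's figure with 45% versus 55%**

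- λ = 0.1597 and 0.1196; HR = 0.749; |ln HR| = 0.2894.
- P = 0.757 × (1 − 0.235) = 0.579 for control and 0.700 × (1 − 0.308) = 0.484 for radiation.
- d = 280 × 1.063 = 297.6.
- Power = Φ(0.2894 × √74.4 − 1.96) = Φ(0.537) = **70.4%**.
- 70% power needs 295 deaths, which is 295/1.063, or 278 per group.

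Freedman's formula gives 299 deaths, 282 per group and 69.8% power. The stated 280 and 70% lie between the two methods, so they reproduce for a 10-point difference.

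**Step 2. The same trial with a 5-point difference**

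| Comparison | HR | Deaths | Power at 280 per group | Per group for 70% power |
|---|---|---|---|---|
| 45% vs 55% | 0.749 | 298 | 70.4% | 278 |
| 45% vs 50% | 0.868 | 311 | 23.8% | about 1,110 |
| 50% vs 55% | 0.862 | 285 | 23.8% | about 1,110 |

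For 45% versus 50%: |ln HR| = 0.1415, P = 0.579 and 0.532, d = 280 × 1.111 = 311, and power = Φ(0.1415 × √77.8 − 1.96) = Φ(−0.712) = **23.8%**. 70% power needs 1,234 deaths, or 1,234/1.111 = about 1,110 per group.

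**Step 3. Can other assumptions rescue the 5%?** Power for 45% versus 50% at 280 per group:

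- no drop-out: 26.8%
- follow-up fixed at 5 years, without drop-out: 22.8%
- follow-up fixed at 5 years, with drop-out: 20.9%
- two-proportion test at 5 years: 21.9%
- one-sided test: at most about 38%

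None comes near 70%.

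**Step 4. Can another reading rescue the 5%?**

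- *Difference at another time.* Under the exponential model, survival at 7 years is 0.45^(7/5) = 32.7% versus 0.55^(7/5) = 43.3%, and at 9 years 0.45^(9/5) = 23.8% versus 0.55^(9/5) = 34.1%. The gaps are 10.6 and 10.3 points, so reading the primary endpoint as survival at the end of the study does not help.
- *Relative difference.* 55/45 is a 22% relative gain in survival, and the hazard is reduced by 25%. Neither is 5%.

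**The case against.** The strongest case on the other side is that nothing operative is wrong. The sample size, power, test level, drop-out rate and both survival rates fit together. The intention-to-treat analysis and the Cox model use no 5% margin, and no stopping rule depends on the detectable difference. The 5% appears once, beside the two rates that expose it, in a paragraph that also uses 5% for the significance level and for yearly drop-out. It is probably a slip of wording. Corrected, the trial would recruit and analyse the same patients in the same way.

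That is fair, and it limits the finding: it concerns a misstated design effect, not a miscalculated sample size. It does not remove the finding. The detectable difference is a core design figure for the primary endpoint, and it is wrong by a factor of two in the flattering direction.

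Three narrower objections also stand:

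- The article plans no explicit conclusion about a 5-point benefit, so misreading a null result is a risk, not a certainty.
- Accrual pattern and drop-out form are assumptions, so the 24%, the 1,110 and the 298 deaths are approximate. Without drop-out, for example, about 960 per group would suffice for 5 points.
- A protocol need not report power for an effect it was not sized for, so that addition is advisable but not required.

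**Conclusion.** The statement is wrong as written. The 280 per group at 70% power belongs to a 10-point difference in 5-year overall survival (45% versus 55%, hazard ratio about 0.75). For a 5-point difference the power is about 24%, with a range of 21% to 27% across two-sided log-rank variants that follow patients for at least 5 years, and the trial has about a quarter of the patients needed for 70% (280/1,110 = 0.25). The exact values rest on uniform accrual and exponential drop-out; the conclusion does not. That the 5% is the erroneous figure is an inference, but a strong one, because the stated sample size and power fit 10 points and no variant tried brings 5 points near 70%.

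**What to change.** In Randomization and Sample Size, replace the 5% difference with an absolute difference of 10 percentage points in 5-year overall survival (45% versus 55%, hazard ratio about 0.75). If an expected number of deaths is added (about 298), give the accrual and drop-out assumptions with it. It is advisable, though not essential to remove the contradiction, to add that power for a 5-point difference is only about 24%.

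The sponsor should first confirm that 10 points was the intended target. If so, the sample size, significance level and power stay unchanged, and the cost is one sentence and a less favourable stated detectable effect. If 5 points was truly intended, a change of wording is not enough: 70% power would need about 1,110 per group, and feasibility would have to be reconsidered.
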